#### 2.3.1. Inclusion Criteria

Male and female children between 0 and 36 months, with a risk of neurological alteration or diagnosis of cerebral palsy or neuromotor disease, who are admitted for assessment and/or treatment according to the Vojta therapy methodology or conventional treatment in the Physical and Rehabilitation Medicine Service will be included in this study. The diagnosis may be clinical and/or supported by the presence of lesions in complementary tests. Due to the fact that the diagnosis of cerebral palsy is confirmed in many cases after one year of life, the data of children in treatment for risk of neurological alteration will only be included retrospectively when said diagnosis has been confirmed. Younger children have not received a definite diagnosis of CP yet, but, based on the presence of lesions determined by magnetic resonance imaging, their risk of developing CP was estimated to be sufficiently high to justify their inclusion in the CP group. 

Parents or guardians must sign the informed consent that will allow us to use their data on therapeutic results, always in a pseudonymized (coded) way, guaranteeing confidentiality. 

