### 1.1. Hypothesis

“Vojta or Reflex Locomotion therapy improves the rate of development of gross motor function in babies and children with neuromotor disorders”.

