### 1.2. Main Goal

This study aims to demonstrate that there are changes in the motor development of children with cerebral palsy with the application of Vojta therapy by quantifying the impact on the rate of development of gross motor function in children younger than 36 months of age with neuromotor disorders.

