### 2.2. Study Location

The study will be carried out in the Physical Medicine and Rehabilitation Service of the Teresa Herrera Maternal and Child Hospital of the A Coruña and Cee Health Area. Further sites may be joining the recruitment once their approvals are finalized. The study will be conducted between January 2024 and December 2024 in the Physical Medicine and Rehabilitation Service of the Teresa Herrera Maternal and Child Hospital of the A Coruña and Cee Health Area.

The data collected will pertain to subjects at risk of neurological alteration or diagnosis of cerebral palsy or neuromotor disease, who are admitted for assessment and/or physiotherapy treatment. Following the usual clinical practice protocol, the children will be assigned to one of the physiotherapists who apply Vojta therapy (patients who will be considered as the intervention group) or to a physiotherapist who applies conventional treatment (patients who will be considered as the control group).

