#### 2.3.2. Exclusion Criteria

The data of those patients who have had to apply another therapy (pharmacological, surgical, or rehabilitative) during the care provided by the physiotherapist in their usual clinical practice will not be included. For ethical reasons, this will not be explicitly explained to the families who agree to participate in this study, so as not to influence possible therapeutic decisions in the following two months. Data of the children will be followed up and can be excluded later if there is a change in their diagnosis and cerebral palsy is not confirmed at the appropriate age. The previous therapeutic trajectory, as well as concomitant treatment (such as pharmacological treatment for spasticity, dystonia, epilepsy, etc., as well as other rehabilitation interventions) was not considered within the exclusion criteria for two reasons: their effect would already be included within the rate of motor development before VT, and also because all the children were compared only to themselves. These will be noted and considered during the calculations, but the data exclusion will only occur if there are changes in them (both adding or withdrawal) during our 2 months of intervention. 

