### 2.4. Outcomes

Two of the most accepted scales in pediatric rehabilitation will be used, quantifying gross motor function from different aspects.

The first is the Gross Motor Function Measure (GMFM). Gross motor function and mobility have important roles for classification, assessment, and research involving children with neuromotor disorders [42,43,44]. The Gross Motor Function Measure [45] could be currently considered as gold standard for the quantification of gross motor function in the pediatric rehabilitation. These follow ups of thousands of children with cerebral palsy described the long-term development of their gross motor function and defined five unalterable levels of severity. By the age of six, stability over time on the prognosticated level of mobility is expected [45]. Even though the GMFM was not designed to assess outcomes of therapeutic interventions, some authors have used its centiles to compare individual effects. The use of the reference percentiles for the GMFM as outcome make it possible to estimate the change between two subsequent assessments and to directly compare gross motor improvement across ages and Gross Motor Function Classification System (GMFCS) levels. On the other hand, uncompleted items of GMFM assessments are used as short-term therapeutic goals and, therefore, individually controlled comparison of the rate of acquisition of gross motor function seems to be possible within each range. 

The Infant Motor Profile (IMP) scale [46] is another evidence-based method of assessing infant motor behavior. It not only quantifies motor milestones, but also tests movement quality by analyzing five factors: variability, adaptation, symmetry, fluency, and capacity. The advantage of this scale is that the assessment is performed through video recording, allowing us to have a dedicated clinical evaluator blinded to the type of intervention. 

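### The protocol does not hold to one target population: entry criteria, later exclusion and stated claim differ on whether neuromotor disease other than cerebral palsy counts

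*Protocol article*

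**What the plan says.** **Entry.** Section 2.3.1 takes children aged 0 to 36 months "with a risk of neurological alteration or diagnosis of cerebral palsy or neuromotor disease, who are admitted for assessment and/or treatment". Section 2.2 gives the same three routes: "subjects at risk of neurological alteration or diagnosis of cerebral palsy or neuromotor disease".

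**Children without a diagnosis.** Section 2.3.1 then says that the data of children treated because of neurological risk "will only be included retrospectively when said diagnosis has been confirmed"; the diagnosis meant is CP. The next sentence says of younger children with lesions on magnetic resonance imaging (MRI) that "their risk of developing CP was estimated to be sufficiently high to justify their inclusion in the CP group".

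**Later exclusion.** Under section 2.3.2, children are followed up and their data "can be excluded later if there is a change in their diagnosis and cerebral palsy is not confirmed at the appropriate age".

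**The claim.** The hypothesis in section 1.1 is that the therapy "improves the rate of development of gross motor function in babies and children with neuromotor disorders". The main goal in section 1.2 is to show that "there are changes in the motor development of children with cerebral palsy with the application of Vojta therapy", and the same sentence goes on to name neuromotor disorders as the population. The abstract describes a trial in patients with CP, and section 2.6 cites only a CP prevalence (2.08 per 1000 births).

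**The concern.** A trial population is defined by who enters, who is analysed and about whom the conclusion is drawn. Here the three do not match. Entry is broad, the rules for keeping data refer only to CP, and the claim moves between the two.

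Two things are at stake. The first is interpretation: a reader cannot tell whether the result will describe children with CP or a wider group. The second is bias: where the analysed set depends on a diagnosis settled after assignment, and on a rule that permits exclusion without requiring it, the make-up of the two groups can be altered after treatment has started. Section 2.1 says that neither the therapists nor the assessors of the Gross Motor Function Measure (GMFM) can be blinded. The article does not say who takes the exclusion decision, or with what knowledge of group and outcome.

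**Working it through.** No figure decides this point, so the check sets the sections side by side.

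**Step 1. Which population does each place name?**

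| Place in the article | Population named |
|---|---|
| Title; 1.1 Hypothesis; 1.3 Secondary Goals | Neuromotor disorders or alterations |
| Abstract (objective and design); 2.6 (prevalence) | CP |
| 1 Introduction, last paragraph | Hypothesis sentence: neuromotor disorders; purpose sentence: CP |
| 1.2 Main Goal | Both, in one sentence |
| 2.2 and 2.3.1 (entry) | At risk, or CP, or neuromotor disease |
| 2.3.1 (at-risk children) and 2.3.2 (later exclusion) | CP is the only diagnosis that confirms a child |

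**Step 2. What does the exclusion rule require?** It joins two conditions, a changed diagnosis and CP not confirmed, and it is permissive. The confirmation condition in section 2.3.1 is addressed only to children treated because of risk.

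**Step 3. Apply the rules to children who end with the same non-CP neuromotor disease.**

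| Label at entry | Rule that applies | Result |
|---|---|---|
| Established non-CP neuromotor disease, unchanged | Entry route met; no change in diagnosis | Stays in |
| At risk, awaiting diagnosis | 2.3.1: counts only once CP is confirmed | Left out |
| At risk, already placed in the CP group on MRI lesions | 2.3.2: diagnosis changes, CP not confirmed | May be dropped or kept |
| CP, later revised | 2.3.2: diagnosis changes, CP not confirmed | May be dropped or kept |

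The same final diagnosis thus has three possible outcomes, depending on the label at entry and on a later choice.

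**Step 4. When is that choice made?** Section 2.3.1 says that CP is in many cases confirmed after one year of life. Section 3 places the second assessment at 2 months (±1 week). Taking confirmation at 12 months or later, a child whose initial assessment falls before about 12 − 2 = 10 months of age has the outcome measured before the diagnosis is settled. Entry runs from 0 to 36 months, so such children are within the planned sample. For them the exclusion decision can follow the result.

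**Step 5. Size.** The article gives no share of children with a non-CP diagnosis and no share of at-risk children who fail confirmation. Neither a loss of numbers nor a bias can be computed from it.

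**The case against.** The strongest reply is that the eligibility rules can be read coherently. Children with diagnosed CP or diagnosed neuromotor disease enter, at-risk children count once CP is confirmed, and a child whose label changes may be removed. On that reading nothing shuts out a child with a stable non-CP disease. This stands, and it rules out a stronger inference that a reader might draw: that the exclusion criteria remove all non-CP children, so that the trial cannot support its claim. The two joined conditions do not reach an established, unchanged diagnosis.

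A reader might also infer that a CP-only analysis would leave the hypothesis without any analysed children. That fails too. The article treats CP as one of the neuromotor disorders, so the claim would be broader than the data but not empty.

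A third inference would be a definite loss from the 30 children per group. The documents do not support it, because no share is given and section 2.6 does not say whether the 30 are counted before or after exclusions.

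On measurement, section 2.4 describes the GMFM severity levels from CP cohorts ("These follow ups of thousands of children with cerebral palsy described the long-term development of their gross motor function"). The same section also speaks of neuromotor disorders generally, and the rate and acceleration formulas in sections 2.6 and 4 do not use those levels. The choice of scale therefore adds little to this point.

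Finally, section 2.3.2 argues that each child is compared only with itself, which might seem to make the mix of diagnoses unimportant. However, the Statistical Methods section plans a repeated-measures analysis of variance with treatment group as a factor, so who remains in each group still matters.

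The coherent reading does not remove the defect. It is the reading under which the same disease is kept or lost according to the entry label, and under which the abstract's description of the patients is incomplete.

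**Conclusion.** The point holds as an inconsistency in the target population, joined to a discretionary exclusion after assignment. It should be corrected, because it changes who is analysed and what may be concluded. It does not show that the trial is unable to answer its question.

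The conclusion rests on the literal text of sections 2.2, 2.3.1 and 2.3.2, and on reading the neuromotor-disease route as including diseases other than CP, which the wording sets beside CP as an alternative. The timing argument assumes confirmation at 12 months or later; the article says this of many children, not all. The size is unknown. If few non-CP children are referred and few at-risk children fail confirmation, the effect on the comparison will be small and the main problem will be the wording of the claim.

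This is not a detail that can be left to an analysis plan or that a short article merely omits. The entry, exclusion and hypothesis statements are all present, and they disagree.

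**What to change.** Reconcile the title, the abstract, the last paragraph of the Introduction, and sections 1.1 to 1.3, 2.2, 2.3.1 and 2.3.2 to one population, fixed at the initial assessment. Two routes are open:

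- **(a) Narrow.** Restrict entry to diagnosed CP or high risk of CP by the MRI-lesion criterion already in section 2.3.1. Delete the neuromotor-disease route, and word the title, hypothesis and goals for that population.
- **(b) Broad.** Keep the wider entry, apply the CP-confirmation condition to no child, and report confirmed CP as a prespecified subgroup. Amend the abstract and the purpose statement to match.

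Under either route, replace the optional exclusion in section 2.3.2 with a rule that leaves no discretion and is applied identically in both groups.

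The cost is mainly redrafting. Route (a) brings a somewhat smaller referral pool and a narrower claim; route (b) brings a more mixed sample. Section 4 reports completed assessments for only four children so far, so the change is cheap if made now.

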## 3. Methods and Timeline

Phase 1. Initial Assessment: Children who go to the rehabilitation center where they have been referred will be treated, an initial routine clinical examination will be performed, including: Personal/medical data collection.GMFM quantification.Treatment with the physiotherapist.Training of the parents in the home program.Recording for the IMP quantification.

Phase 2. Intervention period (2 months): The assignment to the therapist will be randomized according to the needs of the service, where each therapist will adapt the treatment according to the initial assessment. Both assessors and therapist cannot be blinded to the allocation or treatment, and both required live-direct performance. An external assessor (blind to both) will be able to score the IMP recordings. 

Children will receive weekly or fortnightly treatment, and their parents, family members, or carer will be trained in carrying out a home program. Each therapist will adapt the treatment according to the initial evaluation, as is usually performed in the rehabilitation service. During the treatment sessions, the physiotherapist will apply the therapy directly, either based on Vojta therapy or conventional physiotherapy. The frequency of repetition of the treatment at home and in the hospital will be recorded, depending on the availability of each family and the normal functioning of the service.

Phase 3. Second assessment at 2 months (±1 week, depending on follow up appointments).

Collection of data on the possible changes made in previous treatments and the frequency of home treatment (possible incidents due to illness or family limitations).GMFM quantification.Recording necessary for IMP quantification.

Children carried on clinically with the intervention, but this short period would allow us to attribute changes to RL, controlling better the influence of other factor (such as age maturation or other therapy inputs).

Study length. The data collection will be carried out for 4 years from the approval of the CEI. Only patients receiving healthcare with any of the therapies under investigation after authorization by the CEI will be included.

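### Sections 2.3.1 and 2.3.2 do not settle whether infants with MRI lesions but no confirmed cerebral palsy belong in the analysis, and the choice could be made with outcomes known

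*Protocol article*

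**What the plan says.** Four statements in the protocol article bear on who is analysed.

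- **Opening criterion, section 2.3.1.** It admits "Male and female children between 0 and 36 months, with a risk of neurological alteration or diagnosis of cerebral palsy or neuromotor disease". Risk alone is enough, and so is neuromotor disease other than cerebral palsy.
- **Wait-for-confirmation rule, section 2.3.1.** Because "the diagnosis of cerebral palsy is confirmed in many cases after one year of life", the section adds that data of at-risk children "will only be included retrospectively when said diagnosis has been confirmed".
- **MRI-risk rule, the next sentence of section 2.3.1.** "Younger children have not received a definite diagnosis of CP yet", but on the strength of MRI lesions "their risk of developing CP was estimated to be sufficiently high to justify their inclusion in the CP group".
- **Later removal, section 2.3.2.** Children are followed up, and their data "can be excluded later if there is a change in their diagnosis and cerebral palsy is not confirmed at the appropriate age".

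Three other facts matter. The second assessment is at 2 months, give or take a week (section 3). Therapists and GMFM evaluators know the treatment, while the IMP is scored blind from video (section 2.1). The planned size is 30 children per group (section 2.6).

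**The concern.** The second and third statements give opposite answers for the same child: an at-risk infant with a lesion on MRI and no confirmed diagnosis. The word *only* in the first of them leaves no room for the other, and nothing says which prevails.

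Two things are at stake. The first is the target population. A comparison among children with confirmed cerebral palsy answers a different question from one among high-risk infants, and section 1.2 itself speaks both of cerebral palsy and of neuromotor disorders. The second is the integrity of the comparison. The children in doubt are the youngest. Their rates are scores divided by the smallest ages (section 2.6 and the Discussion), so group means are sensitive to whether they are counted. If that is decided late, it can be decided by people who know both the group and the GMFM result.

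**Working it through.** The point is a conflict in the text. The plan gives no figure for it, so there is none to reproduce.

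**1. The rules side by side**

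| Child's status at analysis | Wait-for-confirmation rule | MRI-risk rule | Later removal (2.3.2) |
|---|---|---|---|
| Cerebral palsy confirmed | in | in | stays |
| Lesion-positive, diagnosis still open | **out** | **in** | stays unless the diagnosis changes; no age given |
| Lesion-positive, cerebral palsy ruled out | out | in | may be removed, not must be |
| At risk, no lesion, diagnosis open | out | not covered | stays, if ever admitted |

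The direct conflict is in the second row. In the third row, section 2.3.2 closes the gap if it is always applied, but its wording does not require that. In the fourth row the MRI-risk sentence does not apply; the tension there is between the wait-for-confirmation rule and the opening criterion.

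**2. Order of outcome and eligibility**

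A child entering at age *a* months has the second assessment at *a* + 2. If confirmation comes at 12 months or later, the outcome comes first whenever *a* + 2 < 12, that is *a* < 10. Later confirmation widens this range. The document gives no age distribution. If entry ages were uniform over 0 to 36 months (assumption), the share entering before 10 months would be 10/36 = 28%, or 60 × 10/36 ≈ 17 children. That counts children whose outcome could precede confirmation. It does not count children still unresolved at analysis, and not all of them would have a lesion.

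**3. What a choice after results could do (illustration)**

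Assumptions: 30 per arm, no true difference, normally distributed outcomes, a two-sided two-sample t-test at 0.05, the same number of unresolved children in each arm, and unresolved children no different from the rest. With two groups and two time points, the group-by-time test of the planned repeated-measures ANOVA is equivalent to a t-test on change scores. The trial counts as positive if either the all-children or the confirmed-only analysis is significant. There were 40,000 simulated trials per row.

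| Assumed unresolved share | Children left if confirmed only | Type I error if either set may be chosen |
|---|---|---|
| 10% | 54 | 6.2% |
| 20% | 48 | 7.2% |
| 28% | 44 | 7.3% |
| 40% | 36 | 8.0% |
| 50% | 30 | 8.2% |

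Numbers removed are rounded to whole children per arm. Each row treats every unresolved child as one on whom the rules disagree, so it overstates the effect for that share if some have no lesion. It does not include any bias from unequal numbers of unresolved infants in the two arms.

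**The case against.** The best defence is that the sentences describe stages of one process: infants with lesions enter provisionally, their data count once cerebral palsy is confirmed, and they leave if it is not. Section 2.3.2 supports this reading, and if removal were always applied, children in whom cerebral palsy is ruled out would be treated alike under both rules. This part stands, and it narrows the point. It does not remove it: removal is optional, the age is undefined, and a child whose diagnosis is open when the data are analysed remains in one set and outside the other.

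Time also helps. Section 3 foresees four years of data collection, in which many diagnoses would resolve. The abstract and section 2.2, however, end the study in December 2024, so infants recruited late may not be resolved.

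Three stronger readings are tempting and are not supported:

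- A reader might infer that all unconfirmed children are in dispute. The MRI-risk sentence reaches only those with lesions.
- A reader might infer that the sponsor intends to select on outcome. Section 2.3.2 ties removal to a change of diagnosis, which is a clinical event. The text leaves the opportunity open but does not plan to use it.
- A reader might infer that the entry route will go unrecorded because no imaging item is listed. Diagnosis and medical data are collected, and itemised fields belong in a data collection notebook that is not shown.

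**Conclusion.** The point holds for at-risk infants with MRI lesions and no confirmed cerebral palsy. Section 2.3.1 contradicts itself on them, and section 2.3.2 bridges the gap only in part. It should be corrected before analysis, because it defines the population and because membership can be settled after an unblinded outcome is known.

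Its size cannot be derived from the document, which gives neither the share unconfirmed at entry, nor the share with lesions, nor the share unresolved at analysis. The rise in type I error to about 6% to 8% rests on an assumed 10% to 50% unresolved and on a results-driven choice of set. If the rule were fixed beforehand, or every diagnosis resolved and removal applied uniformly, this inflation would not arise. Bias between arms would need an imbalance in such children or a choice made in the light of results; the text makes either possible but shows neither.

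**What to change.** Reconcile section 2.3.1, including its opening criterion, and section 2.3.2 into one rule for membership of the analysis set.

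- **Main analysis.** Preferably base membership only on status recorded at the initial assessment. Every consented child who met the entry criterion on that date stays in the group assigned, whatever the later diagnosis. State explicitly whether at-risk children without a lesion and children with neuromotor disease other than cerebral palsy meet the criterion, so that neither group is dropped by silence. Delete the retrospective-inclusion sentence and the removal for unconfirmed diagnosis.
- **Record.** Enter each child's status at the initial assessment as confirmed or at-risk.
- **Sensitivity analysis.** Repeat the comparison in children with confirmed cerebral palsy only. Judge confirmation at a stated age and by a stated cut-off date, by someone blind to group and outcome.

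If the sponsor wants confirmed cerebral palsy as the main population, the same age, cut-off date and blinded judgement would have to govern the main analysis, with a stated rule for children still open at the cut-off. That also removes the contradiction, at the price of excluding children after assignment.

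The cost of the preferred version is a wording change in two sections and one recorded field. Only four subjects had completed assessments when the article was written, so little needs to be filled in from records. The downside is that some children in the main analysis will turn out not to have cerebral palsy; the sensitivity analysis shows how much that matters.
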